## Abstract

**Background:**

Bruxism is a repetitive activity that causes tooth wear, audible sounds, and discomfort. Preventive measures have been studied for conditions that can exert a negative influence on physiological development in children. Low-level laser therapy administered over acupoints is an effective, painless, low-cost treatment option that has achieved good results. Thus, the aim of the proposed study is to evaluate changes in muscle activity, bite force and salivary cortisol in children with bruxism after the application of low-level laser to accupoints.

**Methods:**

The children will be randomly allocated to four groups of 19 individuals: G1 - low-level laser; G2 - occlusal splint; G3 - placebo laser; and G4 - control (without bruxism). The BTS TMJOINT electromyography will be used to determine muscle activity and a digital gnathodynamometer will be used to measure bite force. Salivary cortisol will be analysed at baseline as well as one and six months after treatment. Two-way ANOVA will be employed and complemented by Tukey’s test.

**Discussion:**

Bruxism is a repetitive activity of the masticatory muscles that can have negative consequences if not treated, such as tooth wear, noises, discomfort and anxiety. Thus, control and treatment measures should be taken. Although low-level laser therapy over acupoints has been indicated for children, the effects of this treatment modality have not yet been studied.

**Trial registration:**

NCT02757261 on 8 April 2016. This study protocol received a grant from the Brazilian fostering agency São Paulo Research Foundation (FAPESP: #2015/24731-0).

**Electronic supplementary material:**

The online version of this article (doi:10.1186/s12906-017-1905-y) contains supplementary material, which is available to authorized users.

## Background

Bruxism is a repetitive activity of the masticatory muscles characterised by grinding and/or clenching one’s teeth or movements of the mandible [1–3]. This condition is classified as either primary or secondary [1]. With primary bruxism, there is no evident medical, systemic or psychiatric cause, whereas secondary bruxism is associated with a clinical, neurological or psychiatric disorder, iatrogenic factors or sleep disorder [1, 4]. Awake (or diurnal) bruxism is characterised by clenching one’s teeth during waking hours and sleep bruxism is the unconscious activity of grinding or clenching one’s teeth during sleep with the production of audible sounds [1, 4–6].

Divergent opinions are found on the aetiology of sleep bruxism. Some authors state that central disturbances are the main cause. In this theory, muscle hyperactivity is caused by instability in the basal ganglia; synapses change the way that they function, altering between inhibitory and excitatory neurons [7]. Another theory assumes that malocclusion is the primary cause of grinding and clenching the teeth, as occlusal maladjustment reduces masticatory muscle tone; with occlusal imbalance, the activity of motor neurons of the masticatory muscles could be initiated by periodontal receptors [7]. Sleep bruxism can be measured using an index score (e.g., rhythmic masticatory muscle activity [RMMA]). Such indices measure the number of bruxism episodes per hour of sleep. The Tooth Wear Index quantifies occlusal and incisal wear to determine its severity and prevalence, with a particular cut-off point considered indicative of sleep bruxism [8]. There is also the theory that orofacial pain stems from a lack of adequate rest time between muscle activities, which leads to muscle overload and pain; however, some authors have failed to prove this [9]. Bruxism is also widely associated with stress and anxiety [10–13].

The frequency of bruxism is high in childhood, with prevalence rates ranging from 13.5 to 33% [14, 15] and this condition can cause harm to the stomatognathic system. Childhood bruxism is difficult to diagnosis and ideal treatment has not yet been established. Physical therapy is currently used to treat this condition and the most commonly employed methods are transcutaneous neuromuscular stimulation, microcurrent electrical neuromuscular stimulation, cryotherapy, ultrasound, infrared therapy, kinesiotherapy, massage therapy, acupuncture, low-level laser therapy (LLLT) and occusal splint usage [16, 17]. According to Solberg et al. [18], an occlusal splint reduces muscle activity and provides greater patient comfort. Occlusal splint usage seems to reduce tooth grinding, masticatory muscle activity and orofacial pain [19]. Although occlusal splints are widely employed for the treatment of bruxism, no specific strategy has been established for the cure of this condition. Thus, further studies are needed [18, 20].

LLLT is a non-invasive, low-cost treatment. The irradiation of trigger points constitutes effective treatment for orofacial pain as well as the reduction of swelling and hyperemia [21]. Acupuncture has also been successfully used for the treatment of bruxism, achieving a reduction in the activity of the masseter and anterior temporal muscles as well as a reduction of anxiety [22]. The stimulation of particular acupoints can alter blood circulation dynamics and promote muscle relaxation, thereby alleviating muscle spasms, inflammation and pain. Moreover, such stimulation leads to the release of hormones, such as cortisol and endorphins, thereby promoting an analgesic effect [23]. The stimulation of acupoints can be achieved with the use of needles, infrared irradiation, electrical current or laser [24]. The latter method is indicated for children because it is painless and has a shorter exposure time per acupoint [25–27]. However, the use of LLLT over acupoints has not yet been tested on children with bruxism. Therefore, the aim of the proposed study is to investigate changes in maximum bite force (measured using a gnatodynamometer) one and six months after low-level laser therapy over acupoints and occlusal splint usage compared to muscle hyperactivity at baseline in children. The secondary outcomes are the measure of pain (VAS scale), muscle activity (using the BTS TMJOINT® electromyograph) and salivary cortisol.

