### Statistical analyses

Descriptive statistics will be used first for the determination of point estimates. The Shapiro-Wilk test will be used to determine the normality of the data. The chi-square test, Student’s t-test and ANOVA will be employed for the analysis of associations between variables, with the level of significance set at 5% (*p* < 0.05). After the analysis of data distribution, ANOVA will be used for the evaluation of residuals and parametric tests will be used for the determination of pre-treatment conditions. Interval estimates will be used for the variables of interest to determine the estimates and perform comparisons. When necessary, transformation methods or non-parametric tests will be used in the data analysis.

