## Discussion

The main objective of the proposed study is to compare the efficacy of low-level laser therapy administrated to acupoints and occlusal splint usage in children with bruxism. Obviously, it will not be possible to blind the participants submitted to occlusal splint usage (G2), as will occur with the other treatments (G1, G3 and G4), which can be considered a limitation of the study. However, this treatment cannot be excluded, since it is the gold standard in the literature, despite divergences of opinion [37].

Regarding the outcome variables, methods will be employed that can be reproducible in future studies and accessible to patients. Although polysomnography (sleep study) is the most effective for the diagnosis of bruxism, this method has limitations, such as the high cost and the amount of time required for its execution [38]. Moreover, this method had been criticised due to the fact that the patient is not in a familiar environment and children normally do not cooperate, which compromises the quality of the test [38].

The outcome variables muscle activity and bite force have been validated and used in previous studies [8, 39]. We expect an improvement in the distribution of the contact symmetry based on the chosen acupoints (regulation of anxiety/muscle relaxation). We do not expect the number of contacts to increase or intensify nor do we expect any improvement in the bruxism index (which will not be measured in this study). Some acupuncture points, especially IG-4 (Hegu), F-3 (Taichong) and BP-6 (Sanyinjiao), are indicated to alleviate anxiety and VB-34 (Yanglingquan) is used to treat muscle contraction.

The third outcome (level of salivary cortisol) has become increasingly common due to its non-invasive nature and the existence of accessible commercial kits [40–42]. We will act on some anxiety points, especially IG-4 (Hegu), F-3 (Taichong) and BP-6 (Sanyinjiao). Some authors [43, 44] state that benzodiazepines, especially clonazepam, are beneficial to adult patients with bruxism. However, the risk of dependency limits its use for prolonged periods. Moreover, such therapies are not indicated for children due to the side effects [45]. We expect treatment with acupoints to improve the anxiety of these children and cause a decrease of cortisol levels. While the attention given to the children during treatment could have a positive effect on decreasing anxiety, all groups will be subject to this bias.

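### The stated aim sets bite force against a different baseline variable, the Discussion gives a different main comparison, and neither names the placebo arm

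*Protocol article*

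**What the plan says.** The Background of the protocol article says that "the aim of the proposed study is to investigate changes in maximum bite force" and continues with "one and six months after low-level laser therapy over acupoints and occlusal splint usage compared to muscle hyperactivity at baseline in children". The next sentence reads "The secondary outcomes are the measure of pain (VAS scale), muscle activity" and adds salivary cortisol. Bite force is therefore the main outcome by implication, although the word primary is not used.

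The Discussion says: "The main objective of the proposed study is to compare the efficacy of low-level laser therapy administrated to acupoints and occlusal splint usage". It names no outcome in that sentence.

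On analysis, the abstract describes four groups and says "Two-way ANOVA will be employed and complemented by" Tukey's test. The Statistical analyses section lists chi-square, t-test and ANOVA. Neither place singles out a contrast.

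Under Randomisation and interventions, G1 is the experimental arm (laser), G2 the positive control (splint), G3 a control (placebo laser) and G4 a control made up of children without bruxism.

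**The concern.** The aim sentence cannot be analysed as written, because a change in bite force has no meaning relative to the starting level of an EMG measure. If the phrase is read generously as each child's state before treatment, the sentence describes a before-after comparison. The Discussion describes a comparison between two treatments. These are different estimands and can give different answers from the same data.

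The children are six to eight years old, and the Background places the last assessment six months after treatment. Within one arm, a change over that time mixes any treatment effect with growth. It also includes regression to the mean, to the extent that selection on tooth wear and parental report also selects on bite force. A between-group contrast among randomised children removes both in expectation.

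G3 receives the same device with guide light and sound but no energy, so laser versus placebo is the contrast that isolates the laser. The Randomisation section also has the switched-off device positioned in G2, but those children wear a splint, and the Discussion concedes that they cannot be blinded. The stated aims leave G3 without a role.

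**Working it through.** **Step 1. The statements side by side.**

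| Place | Outcome | Comparison | Names G3? |
|---|---|---|---|
| Background, aim | Maximum bite force | Laser and splint, each against a baseline muscle measure | No |
| Discussion, main objective | None named | Laser versus splint | No |
| Abstract, Methods | None named | Four groups, two-way ANOVA with Tukey | Only as one of four |

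The first two rows are objectives and they disagree. The third is a method of analysis and does not choose between them. The abstract's aim does not settle it either: it is to "evaluate changes in muscle activity, bite force and salivary cortisol in children with bruxism after the application of low-level laser to accupoints", with three outcomes together and no comparator.

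**Step 2. Does the sample size show which contrast was meant?** The dropout step reproduces: 15.75 × 1.2 = 18.9, hence 19. The section names no outcome, contrast or mean difference. The 15.75 agrees with 2(1.960 + 0.842)²/d² = 15.70 at d = 1.0, a two-sided comparison of two groups about 1 SD apart. It would also fit a four-group F test with f = 0.43. Neither effect size is stated, so the calculation does not identify the deciding contrast.

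**Step 3. Which visits could carry the comparison?** Study variables puts bite force at baseline and at one and six months after treatment. The bite force protocol puts it before treatment, at the end of treatment and 30 days later. Taking one month as 30 days, the only post-treatment visit on which both agree is about one month after treatment. The intervention text also says that G3 receives complementary treatment after 30 days of follow-up. A six-month comparison with G3 would therefore not be with an untreated group.

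**Step 4. What the Tukey family costs (illustration only).** Assume that 15.75 per group was for one two-group t-test, two-sided 5%, 80% power. With df = 2 × 15.75 − 2 = 29.5 and critical t = 2.044, the noncentral t gives d = 1.032.

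For any pair, the noncentrality is d√(n/2): 1.032 × √7.875 = 2.90 at n = 15.75, and 1.032 × √9.5 = 3.18 at n = 19. The Tukey critical value is q(0.95; k, k(n − 1))/√2 for k groups.

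| Family | Critical t, n = 15.75 | Power, n = 15.75 | Power, n = 19 |
|---|---|---|---|
| One named contrast, two groups only | 2.044 | 80.0% | 87.2% |
| Tukey, G1 to G3 (k = 3) | 2.425 | 68.1% | 77.7% |
| Tukey, G1 to G4 (k = 4) | 2.644 | 60.1% | 70.8% |

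At n = 15.75 the loss from one named contrast to the four-group family is 80.0 − 60.1 = 19.9 points. With the error variance pooled over four groups (df 59, critical t 2.001), the single contrast has 81.3% and the loss is 21.2 points. The part due to G4 is 68.1 − 60.1 = 8.0 points. The rest comes from comparing the three bruxism arms with each other.

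**The case against.** The strongest reply is that the Background sentence is only loosely worded. Methods calls the trial randomised and controlled, the groups are labelled experimental, positive control and control, and a multi-group ANOVA is planned. The Background uses muscle hyperactivity when describing how bruxism arises, so the phrase may simply mean the bruxism state at entry. Baseline bite force is measured, and concurrent groups on the same schedule would reveal time trends. The children are also trained on the device beforehand, which limits a practice effect. All of this stands: a between-group analysis is probably intended and the data would support it. It does not remove the disagreement between the two stated objectives, or the absence of G3 from both.

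Four stronger readings are tempting and are not supported.

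- A reader might count the ANOVA with Tukey as a third competing objective. It is an analysis, and a group-by-time model could serve either objective.
- A reader might infer an inflated false positive rate from repeated before-after tests. The two arms in the Background sentence at two visits would give 1 − 0.95⁴ = 18.5% under independence. No section schedules such tests, and two visits in one arm share a baseline, so they are not independent. Tukey's test would itself control multiplicity over the pairs.
- A reader might blame the whole loss of power on G4. In the illustration it accounts for about 8 of some 20 points.
- A reader might conclude that laser versus splint should be tested only if laser beats placebo. The Discussion makes laser versus splint the main objective, and such a rule could leave it formally untested. The order is for the investigators to choose.

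**Conclusion.** The point holds as a contradiction in the text, not as detail left to an analysis plan. The aim names the wrong reference variable for bite force, the two statements of the main question differ, and the placebo arm appears in neither. G4 sits in the Tukey family, although children with bruxism cannot be randomised to a group defined by its absence.

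The bias from a before-after reading is real in direction of reasoning but cannot be quantified here, because the documents give no figures for growth or repeatability of bite force. The power figures rest on three assumptions: that 15.75 was for a single two-group comparison, that Tukey covers all pairs, and that the test is two-sided. They show an order of size and do not predict this trial's power. The protocol should be corrected; the design need not change.

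**What to change.** 1. In the Background, replace the muscle measure with each child's own baseline bite force.
2. Reconcile Background and Discussion to one between-group comparison, for example: difference in mean maximum bite force between G1 and the chosen comparator at one named visit, by analysis of covariance with baseline bite force as covariate.
3. State the roles of G1 versus G2 and G1 versus G3 explicitly, in an order chosen by the investigators, and report both with 95% confidence intervals.
4. Before naming the visit, reconcile the bite force schedules in Study variables and in the bite force protocol. State how the visit relates to the complementary treatment in G3, since a six-month contrast with G3 is not with an untreated group.
5. Keep G4 as a descriptive reference, outside the Tukey family.

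The cost is wording of the aim and the analysis, with no extra children or visits needed for the comparison itself. The downside is that contrasts with G4 become descriptive.

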## Methods

This is a protocol for a randomised, controlled, clinical trial. The project received approval from the Institutional Review Board of Nove de Julho University (Brazil) under process number 1.333.636. The participants and legal guardians will receive clarifications regarding the objectives and procedures and will sign a statement of informed consent agreeing to participate in the study.

### Sample size calculation

For the calculation of the sample size, the researcher will specify that an increase in the standard deviation of the responses for which the null hypothesis will be rejected is *P* = 20%. Adopting a maximum significance level of α = 0.05 and a minimum test power of 80%, the number of subjects per group will be *n* = 15.75, which will be increased by 20% to compensate for possible dropouts, leading to 19 subjects per group (total: 19 × 4 = 76 subjects).

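### The 15.75 children per group at 80% power cannot be reproduced from the stated 20% increase in SD for four fixed arms, and the power is tied to neither bite force nor any treatment contrast

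*Protocol article*

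**What the plan says.** The section *Sample size calculation* of the protocol article specifies the effect in one clause: "an increase in the standard deviation of the responses for which the null hypothesis will be rejected is" P = 20%. It adds a "maximum significance level of α = 0.05" and "a minimum test power of 80"%, and concludes that "the number of subjects per group will be *n* = 15.75". That number is one "which will be increased by 20% to compensate for possible dropouts, leading to 19 subjects per group", or 76 children in four groups. The section names no outcome, comparison, test, mean difference or SD.

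Elsewhere in the article:
- The closing aim in *Background* is change in maximum bite force, with pain, muscle activity and cortisol as secondary outcomes.
- *Discussion* gives the main objective as laser versus occlusal splint.
- *Randomisation and interventions* names four arms: laser, splint, placebo laser, and children without bruxism.
- The abstract says of the analysis: "Two-way ANOVA will be employed and complemented by" Tukey's test.

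**The concern.** A percentage increase in the SD of responses is a recognisable way to state an ANOVA effect: it says how much the overall SD grows when the differences between group means are added to the within-group scatter. It converts directly to Cohen's f, so the printed n can be checked. For four fixed arms, the check gives about half the printed number.

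The paragraph is the trial's only power statement. If its n does not come from its stated effect, and the effect is not expressed in bite force or as a difference between two treatments, a reader cannot tell what a null laser-placebo or laser-splint result would rule out. The group without bruxism adds to this. It is expected to differ from the others, so it could drive a four-group test and say little about the treatment contrasts.

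**Working it through.** **Inputs.** SD increase P = 20%, α = 0.05, power 80% and n = 15.75 come from *Sample size calculation*. The four groups come from *Randomisation and interventions*, and ANOVA with Tukey's test from the abstract. Sidedness is not stated, and I take two-sided where it matters.

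**1. Fixed-effects ANOVA (suits four named arms).**
- Total SD / within-group SD = 1.20, so f² = 1.20² − 1 = 0.44 and f = 0.663.
- Power = P[F′(k−1, k(n−1); λ) > F crit], with λ = k·n·f².
- k = 4: 80% power at n = 7.25, so 8 per group. For k = 3 it is 8.38, and for k = 2 it is 9.98.
- At n = 15.75 and k = 4, λ = 4 × 15.75 × 0.44 = 27.72 on 3 and 59 df, and power is 99.5%.
- In reverse, n = 15.75 gives 80% power at f = 0.430. The SD increase is then √(1 + 0.430²) − 1 ≈ 8.9%, not 20%.

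**2. Random-effects ANOVA, same inputs.**
- Power = P[F(3, 4(n−1)) > F crit / (1 + 0.44n)].
- At n = 15.75, F crit = 2.761 and 1 + 0.44 × 15.75 = 7.93, which gives 79.1% power.
- 80% power needs n = 16.41.

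**3. Other readings.**

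| Reading | n per group |
|---|---|
| F test that one SD is 1.2 times another | 188 one-sided, 238 two-sided |
| 20% taken as a variance increase, k = 4 | 14.64 |
| Two groups, d = 0.2 | 310 one-sided, 393 two-sided (normal formula) |
| Two groups, d = 1.0, normal formula: 2(1.96 + 0.8416)² | 15.70 |

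The variance reading departs from the text, which says SD. The last row needs a 1 SD difference that the section does not state. An exact t test for that difference needs 16.7 per group and has 77.5% power at 15.75.

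**4. What 16 analysable per arm can detect at 80% power (pairwise, noncentral t).**

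| Comparison | df | Critical value | Detectable difference |
|---|---|---|---|
| One two-sided 5% test, no adjustment | 30 | t quantile | 1.02 SD |
| Tukey over the three bruxism arms | 45 | 2.42 | 1.16 SD |
| Tukey over four groups | 60 | 2.64 | 1.24 SD |

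Under four-group Tukey, a 1 SD pairwise difference has 58% power.

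**5. Dropout step.**
- 15.75 × 1.2 = 18.9, so 19 follows as written.
- Keeping 16 of 19 allows 3 losses, 3/19 = 15.8%. Keeping 15.75 allows 1 − 15.75/19 = 17.1%.
- If 20% were lost, 19 × 0.8 = 15.2 would remain. Depending on the model, power would fall by between about 0.8 points (79.1% to 78.2%, random effects) and 1.7 points (80% to 78.3%, fixed effects).

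**The case against.** The strongest defence is that an SD-increase effect size also works with random group effects. On that reading the section's own P, α, power and number of groups give 16.41, within one child per group and one power point of what is printed. This stands as far as it goes: it is wrong to say that no reading of the stated inputs comes near 15.75. It does not settle the matter. The random-effects model treats the arms as a sample from a population of treatments, whereas these are four chosen arms. It powers a variance component, not a difference between two treatments. At 15.75 it is also just below the stated 80% minimum.

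A second defence is that this is a condensed article, and a full derivation with an SD may exist elsewhere. That is fair for the missing detail. But the effect, α, power and n are all printed here, and under the model that suits the design they do not agree.

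A reader might also infer stronger conclusions that the document does not support:
- **That the trial is under-powered for its stated effect.** On the fixed-effects reading it is over-sized for a 20% SD increase. The 58% figure concerns a 1 SD pairwise target used here for illustration, and the section claims no power for Tukey contrasts.
- **That the authors used the 1 SD two-group formula.** The match at 15.70 is close, but nothing in the text shows it was the source.
- **That the dropout allowance fails.** The section says that n is one "which will be increased by 20% to compensate for possible dropouts". It states no expected 20% dropout rate and promises no tolerance of one. The multiplication is right, and a true 20% loss would cost less than two power points.

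**Conclusion.** The point holds as a mismatch between the stated effect, the stated n and the design. For four fixed arms, the 20% SD increase needs 8 per group rather than 15.75, and 15.75 corresponds to an SD increase of about 9%. The close match comes from a model that does not fit the arms. The 80% power is attached neither to maximum bite force nor to a laser-placebo or laser-splint difference, so it cannot be used to interpret a null result on either.

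This rests on reading the 20% as total over within-group SD, on equal group sizes, and on normal, equal-variance responses. The detectable differences further assume 16 analysable children per arm and no gain from baseline adjustment. They cannot be turned into force units, because the article gives no SD for bite force. The dropout arithmetic is a footnote and does not bear on the conclusion.

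**What to change.** Keep 19 per arm and rewrite the paragraph. Remove the 20% SD increase and the 15.75. State the outcome (maximum bite force), the visit, the contrast (laser versus placebo laser, or laser versus splint), and the assumed SD in the device's unit with its source. Then give the detectable difference with 16 analysable per arm, choosing the figure that matches the planned analysis:
- about 1.02 SD for one unadjusted two-sided 5% comparison;
- 1.16 SD if the three bruxism arms are Tukey-adjusted;
- 1.24 SD under four-group Tukey.

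Add that 19 per arm tolerates up to 3 losses (about 16%) while keeping 16.

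The cost is one paragraph and no extra children. The downside is that a detectable difference of 1 SD or more is a less favourable claim than the present wording suggests. If the authors did use a random-effects model, they should say so. They would still need to give the detectable treatment difference, because that model does not supply it.
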